## Abstract

**Background:**

Substance use disorder (SUD) represents a significant public health concern in the United States. SUD recovery is complex and individualized, and support provided by peer recovery coaches (PRCs) can improve outcomes. The PRC-client relationship requires bidirectional mediated communication that is often informal but should be trackable, efficient, and aligned with health care privacy and security regulations. Current workflows and available apps do not meet these needs, illustrating the opportunity for client-centered technology tools. We have developed Peer PLUS (People Leveraging Urgent Support; Parkview Health System, Inc), a HIPAA (Health Insurance Portability and Accountability Act)-compliant mobile app and client management system, to address this need; however, the platform has not yet been tested in a clinical setting.

**Objective:**

We describe the protocol for the evaluation of our digital health platform to identify its perceived usability, potential sustained use, and potential impact on treatment-related outcomes, as well as to assess its feasibility for a future randomized controlled trial and develop an implementation tool kit to facilitate use by other organizations.

**Methods:**

Our evaluation leveraged user-centered design (UCD) and implementation science frameworks (Reach, Effectiveness, Adoption, Implementation, and Maintenance [RE-AIM]). We conducted prelaunch ethnographic observations of 3 PRCs’ workflows for an understanding of user needs. During subsequent in-the-wild testing, PRC-client dyads will use the platform for asynchronous communication within their standard support relationship. We will deploy periodic electronic surveys, including the System Usability Scale (SUS) to assess perceived usability during beta testing, and additional validated measures assessing specific treatment-related outcomes (ie, recovery, quality of care, and therapeutic alliance) during pilot testing. App use log data will be leveraged to assess the likelihood of sustained use. After each test, UCD-focused stakeholder engagements will further elucidate opportunities for platform refinement and implementation tool kit development. Feasibility targets include SUS scores of 68 or more, 25% client eligibility and enrollment rate, and 20% increased contacts between PRCs and enrolled vs nonenrolled clients.

**Results:**

This project was funded in March 2023. Beta test recruitment began in January 2024, with 3 tests completed by November 2024 (3 PRCs and 7 clients). Pilot recruitment began in August 2025. Pilot testing and analyses will continue in 2026. If feasibility metrics are met, the platform will be tested in a later study phase that will include a randomized controlled trial and a second pilot trial to test implementation at a different organization.

**Conclusions:**

Our evaluation assesses whether Peer PLUS is an efficient and usable tool that meets identified communication and documentation needs of clients and PRCs while fostering increased connection, which could suggest the likelihood of sustained use and improved treatment outcomes. This project contributes to the UCD and implementation science fields by demonstrating the importance of merging these frameworks during the design and evaluation of novel digital health solutions.

## Introduction

### Background

Substance use disorders (SUDs) represent a significant public health concern in the United States, with overdose rates increasing continuously over the past 2 decades and, in particular, since the start of the COVID-19 pandemic [1]. The Centers for Disease Control reported a nearly 50% increase in mortality from drug overdose from 2019 to 2021, resulting in a record high of more than 111,000 deaths (age-adjusted rate of 33.6 per 100,000 residents), which remained stable in 2022 before declining slightly in 2023 [2]. Although provisional data suggest a notable drop in overdose deaths in 2024 [3], the spike in mortality during this period of pandemic-related isolation highlighted the importance of social connection in SUD treatment and underscored the need to develop new digital support services to supplement face-to-face care [4]. This is particularly important given that health care systems already struggle to allocate adequate financial and staffing resources to treat individuals with this chronic medical condition, who are additionally at greater risk of other health problems [5,6].

Recovery from SUD is a complex, personal, and individualized process taking place within multiple clinical, social, and interpersonal contexts and necessitating multifaceted, client-centered, and person-focused care [7-10]. In recent years, peer recovery coaches (PRCs) have been increasingly implemented in treatment programs to help address the broad array of challenges faced by individuals in recovery and actively engage them in treatment, which is critical for their long-term success [8,11,12]. These nonclinical staff members extend the reach of treatment into clients’ everyday lives, leveraging their own lived experiences to provide clients with frequent and ongoing tailored support across the 4 dimensions of recovery [8], including emotional and social support as well as connection to clinical resources (eg, medication-assisted treatment) or community agencies that address social determinants of health (Figure 1) [13]. Systematic reviews [7,14-16] suggest positive impacts of peer recovery coaching, such as decreased emergency service use, increased treatment retention, reduced relapse rates, and improved therapeutic alliance; however, these studies also highlight challenges associated with discerning the effects of peer support from other treatment activities that occur in parallel, along with the lack of standardized definitions and outcome measures used across the relevant literature. Given the challenges with sustained funding for PRC programs [17], high-quality research on the effectiveness of PRCs on quality of care and health outcomes is paramount to understanding the impacts of these investments, ensuring their continued financial support.

**Figure 1. F1:**
[figure not shown]
Peer recovery coach–client connection across 4 dimensions of recovery. PRC: peer recovery coach.

### Context

A key tenet of the PRC-client relationship is ongoing connection, often as mediated communication occurring through personal devices [18], especially with the rise of “digital peer support” during the COVID-19 pandemic [19,20]. However, while guidelines emphasize the importance of communication, they do not suggest specific means, methods, or tools [14]. Existing digital recovery support services are limited in that they are either static and nonindividualized or connect clients to informal peer networks but do not provide urgent support integrated with formal care delivery or referrals [21]. Relatedly, while mental health and wellness apps have proliferated in recent years, most are not empirically based, are not specific to SUD, and/or focus too narrowly on relapse rate as a recovery metric [22-26]. Few are successfully integrated into care settings, as this requires intentional execution of usability and implementation strategies (eg, co-design processes, creation of guidelines, and training), as well as a thorough understanding of existing clinical workflows and broader health system contexts (eg, staff buy-in, leadership support, financial considerations, adherence to privacy, and security regulations), and careful consideration of how these factors facilitate or create barriers to uptake and sustained engagement [27-31]. As such, there is an opportunity for a specialized technology tool to facilitate PRC-client communication, with demonstrable efficacy, designed in partnership with users and with implementation and privacy considerations in mind.

To address these challenges and needs, our team proposed the development of a novel platform: Peer PLUS (People Leveraging Urgent Support; Parkview Health System, Inc). PRCs need informal but secure bidirectional communication channels to provide rapid support, along with formal channels to coordinate 24/7 care coverage and document treatment-related data across the PRC team. Peer PLUS meets both of these needs (Figure 2) through a stand-alone HIPAA (Health Insurance Portability and Accountability Act)-compliant mobile app (Figure 3) and its associated web-based client management system (Figure 4). This fills a critical need for a point-of-care mechanism that facilitates and enhances individualized PRC-client communication to foster therapeutic alliance, while also providing an electronic medium to effectively track client engagement and outcomes (eg, referrals to community resources, transfer of information, engagement in treatment, and referral services), as well as allow self-reported client follow-up with external agencies, addressing the legal barrier associated with information sharing between organizations. Our proposal won the 2018 American Hospital Association Innovation Challenge. Funded by this award, we developed wireframes and a low-fidelity prototype of Peer PLUS through an iterative user-centered design (UCD) process involving PRCs and clients, resulting in a functional mobile app that is ready for further evaluation [32]. Table 1 provides a list of key platform features and whether they are available on the client management system, the mobile app, or both.

**Figure 2. F2:**
[figure not shown]
Functions of Peer PLUS platform within the context of the peer recovery coach–client relationship. PLUS: People Leveraging Urgent Support.

**Figure 3. F3:**
[figure not shown]
Design prototypes for Peer PLUS mobile app. PLUS: People Leveraging Urgent Support.

**Figure 4. F4:**
[figure not shown]
Design prototype for Peer PLUS client management system. PLUS: People Leveraging Urgent Support.

**Table 1. T1:** Peer PLUS^a^ platform functionality.

Functionality	Availability		
	Client management system	Mobile app	Both
Add client	✓		
Client information (display and edit)			✓
Share resources			✓
Add new resources			✓
View resource details		✓	
Track use of resources	✓		
Appointment (add, edit, and delete)			✓
Message (send and receive)			✓
Add encounter notes and data	✓		
Track required surveys and data collection	✓		
Adding grants into the system	✓		
Attaching coaches to grants	✓		
Attach coach to a client	✓		
Provide technical support and/or documentation			✓
Send system messages		✓	

a PLUS: People Leveraging Urgent Support.

### Design and Implementation Frameworks

In this study, we will apply an innovative approach that combines frameworks from 2 fields—UCD and implementation science—in the evaluation and refinement of our platform and the development of a robust implementation tool kit. UCD is a design philosophy that promotes early involvement of stakeholders in an iterative process over formative research, design, evaluation, and validation stages [33-35] until a “safe, sound, and desirable” solution is produced [36]. Our team has already taken Peer PLUS through the UCD processes of innovation, understanding users, defining interaction, and design [32]; with this protocol, we now aim to validate Peer PLUS, although we may repeat elements of earlier phases in our refinement of the platform due to the iterative nature of UCD. Implementation science is the study of methods to foster the adoption and integration of evidence-based practices (EBPs), interventions, and other research findings into routine practice, thus enhancing the quality and effectiveness of health care delivery [37]. The Reach, Effectiveness, Adoption, Implementation, and Maintenance (RE-AIM) framework (Figure 5) provides guidance for implementing and evaluating the impact of interventions on health-related behavioral changes across 5 dimensions [38]. The Reach and Effectiveness components focus on recipients of an intervention, while Adoption and Implementation focus on provider and health setting, and Maintenance includes both. We will leverage select elements from each RE-AIM domain to enhance our evaluation, using the RE-AIM Planning Tool to define and operationalize [39]. In addition, we will use the Expert Recommendations for Implementing Change (ERIC) [40] to map barriers to implementation strategies and apply UCD strategies to iteratively refine the design of the app (eg, interviews, think-aloud sessions, and task analysis).

**Figure 5. F5:**
[figure not shown]
RE-AIM processes. RE-AIM: Reach, Effectiveness, Adoption, Implementation, and Maintenance.

Merging of frameworks for a more comprehensive account of the steps involved in successful implementation has been encouraged, as implementation research is important for identifying factors related to integrating EBPs, but inventive strategies (ie, UCD) are often needed to improve the fit of those practices within the real-world clinical context [41,42], such as to address the often-overlooked innovation or intervention domain in implementation frameworks [43]. As such, we aim to identify key UCD strategies that can enhance existing implementation science models to accelerate technology adoption in health care, which will offer a broad contribution to improving the integration and sustained effect of health technology [37,41,42].

### Aims and Contributions

In this study, we propose a robust “in-the-wild” evaluation of our novel technology tool by the platform’s intended users—PRCs and their clients—to assess its usability and its impact on specific client-centered recovery outcomes. Based on the findings of this real-world testing, we will subsequently refine the platform design and develop an implementation tool kit for future deployment. Specific study aims are displayed in Table 2.

**Table 2. T2:** Aims and milestones to be accomplished by the end of the R21 study period.

Aims and objectives	Milestone
Aim 1: Determine if Peer PLUS^a^ is perceived as usable and has sustained use by PRCs^b^ and their clients.	
Refine: Apply UCD^c^ methods and RE-AIM^d^ [38] to refine Peer PLUS and develop an implementation tool kit.	Revised Peer PLUS app Draft implementation tool kit
Usability and feasibility: Validate that Peer PLUS is easy to use and determine if it is likely to have uptake and sustained use in the proposed R33 phase.	Clients and PRCs evaluate Peer PLUS with an average SUS^e^ [44] ≥68 25% of clients approached to participate in the pilot will have a smartphone and consent to participate PRCs connect to clients who are using Peer PLUS 20% more than clients who are not
Aim 2: Evaluate the potential impact of Peer PLUS on recovery, quality of care, and therapeutic alliance between clients and their peer recovery coach during care for SUD^f^.	
Impact: Demonstrate Peer PLUS impact and ability to robustly evaluate the app in the proposed R33 phase.	The following metrics are collected from all clients participating in the pilot SURE^g^ [45] CAHPS^h^ ECHO^i^ [40] WAI-SR^j^ [46,47]

a PLUS: People Leveraging Urgent Support.

b PRC: peer recovery coach.

c UCD: user-centered design.

d RE-AIM: Reach, Effectiveness, Adoption, Implementation, and Maintenance.

e SUS: System Usability Scale.

f SUD: substance use disorder.

g SURE: Substance Use Recovery Evaluator.

h CAHPS: Consumer Assessment of Healthcare Providers and Systems.

i ECHO: Experience of Care and Health Outcomes.

j WAI-SR: Working Alliance Inventory.

This work addresses existing gaps in evidence by (1) collecting outcome data that are indicators of clients’ perspectives of their recovery through standardized instruments [45,48] and (2) using app interaction logs and the Working Alliance Inventory (WAI-SR) [46,47] to discern the impact of PRCs from other recovery treatments [7,14] and to quantify PRC work in support for reimbursement of PRC services [17].

Peer PLUS provides an important alternative to existing recovery apps in 2 ways. For clients, the app uses minimal cellular data and does not require onerous engagement for success; rather, therapeutic alliance with the PRC is the key motivator. For agencies, the platform is not tethered to any clinical group or electronic health record (EHR); rather, the agile modular software architecture and implementation tool kit facilitate integration into site-specific custom workflows, and the companion website allows integrated management of a client panel for care coordination across the PRC team, limiting manual or disparate data tracking and increasing workflow and reporting efficiency. Thus, achievement of the proposed aims will help propel a much-needed, timely method for enhancing communication and connection between PRCs and clients, improving care while also providing an electronic medium to effectively track client engagement and outcomes [14,30].

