## Methods

### Feasibility Objectives and Outcome Measures

This work constitutes the first phase (R21; 2 years) of a 5-year federal research grant from the Agency for Healthcare Research and Quality (AHRQ) to test Peer PLUS, develop an implementation tool kit, and determine whether the tool has sufficient usability and impact to move to the final phase of the grant (R33; randomized clinical trial). The study aims and associated objectives and outcome measures for the present phase are summarized in Table 2.

To accomplish these objectives, in year 1, we will conduct a series of UCD activities, refine the platform, and deploy it with a small sample during beta testing. In year 2, we will continue UCD work, complete further refinement, develop an implementation tool kit, and conduct a pilot study.

For aim 1, we will use UCD methods to refine the functionality of Peer PLUS (eg, develop new features) and apply implementation science frameworks to develop an implementation tool kit. We will validate usability with the 10-item System Usability Scale (SUS) [44] and our own custom user experience survey incorporating RE-AIM elements. We will also measure frequency of use through app interaction logs as a proxy to determine likelihood of sustained use in the proposed R33 phase. Primary outcome measures for the pilot study will include usability ratings (SUS score ≥68; ie, above average) and app usage statistics (20% more connections to clients using the app, compared to contacts with nonparticipating clients, which is documented as standard of care). Based on the client population of the health system, we will target 25% as the proportion of clients approached who are eligible and consent to determine the feasibility of recruiting the target sample size (n=200) for the trial proposed in the R33 phase.

In aim 2, we will assess the platform’s impact on clients through several validated instruments, including the Substance Use Recovery Evaluator (SURE) [45] to assess recovery, the Consumer Assessment of Healthcare Providers and Systems (CAHPS) Experience of Care and Health Outcomes (ECHO) [48] to assess experience with receiving PRC services, and the WAI-SR [46,47] to assess therapeutic alliance. This will demonstrate the ability to robustly evaluate the app in the proposed R33 trial.

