During the beta testing and pilot phases of this study, clients and their PRCs will use the app for asynchronous communication when possible over a period of up to 6 months. Clients and PRCs will be given an instructional overview of the various functions of the app (eg, sending messages, accessing and sharing resources, and setting appointments), and PRCs will send their client a sample message during this introduction, but the dyads will otherwise be instructed to use the app naturally within the context of their existing support relationship. PRCs will additionally use the client management portion of the platform for their existing tasks related to documentation in lieu of their prior workflow, which consisted of a Microsoft Excel spreadsheet. During and after this usage, participants will be surveyed and interviewed about their experience, as detailed below.

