### Statistical Analysis Plan

Data will be analyzed at the aggregate level. To address aim 1 (usability and potential for sustained use), descriptive statistics will be computed on the SUS and recruitment rates to assess whether feasibility targets are met (ie, SUS score ≥68, 25% client eligibility and recruitment rate). Using data collected from the Peer PLUS user log, we will conduct a general categorical analysis as a proxy for end-user engagement. To assess our primary outcome related to client contact, in the pilot trial, we will compare the number and rate of connections to clients using the platform to PRCs’ documentation of contact with nonparticipating clients to determine whether the target of 20% more contacts with enrolled clients was met. Further, to address aim 2 (evaluating the impact of Peer PLUS on treatment-related outcomes), descriptive statistics will be calculated for the SURE, CAHPS ECHO, and WAI-SR survey measures deployed during the pilot trial, which will demonstrate potential improvement related to recovery, quality of care, and therapeutic alliance, as well as the feasibility of using these measures to evaluate the app in the R33 phase.

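### The primary 20% contact milestone is defined by app use in some places and by enrollment in others; the use-based wording can let it be met with no gain among enrolled clients

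*Protocol article*

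**What the plan says.** The Protocol article states the same 20% target in four places, with different groups.

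- **Aims and Contributions, Table 2:** "PRCs connect to clients who are using Peer PLUS 20% more than clients who are not". Both sides are classed by use.
- **Feasibility Objectives and Outcome Measures:** "20% more connections to clients using the app, compared to contacts with nonparticipating clients, which is documented as standard of care". The exposed side is classed by use and the comparator by participation.
- **Abstract, Methods:** "20% increased contacts between PRCs and enrolled vs nonenrolled clients". Both sides are classed by enrollment.
- **Statistical Analysis Plan:** the comparison takes the "number and rate of connections to clients using the platform" and sets it against documented contact with nonparticipating clients, to decide whether "the target of 20% more contacts with enrolled clients was met". One sentence therefore uses both terms for the exposed group.

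The measure is primary. The feasibility section begins its list with "Primary outcome measures for the pilot study will include usability ratings" and then adds app usage statistics, under which it places the contact target. The Statistical Analysis Plan section also calls it a primary outcome. Table 3 ends in a Go/No Go decision for the R33 phase, and the Abstract makes that phase conditional on the feasibility metrics being met.

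On how much the app must be used, the Intervention section says that, after an introduction, "the dyads will otherwise be instructed to use the app naturally within the context of their existing support relationship". The Overview of Study Design asks for use when possible, and the Pilot Procedure asks participants to use the platform. No section sets a minimum for the pilot or says what counts as using.

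**The concern.** An enrolled client who is onboarded but then makes little or no use of the app belongs to the exposed group in the Abstract's wording. Under the wording of the feasibility section, that client is in neither group.

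The difference is not neutral. Messages in the app are contact between a peer recovery coach (PRC) and a client, so choosing the exposed group by app use partly chooses it by the outcome. Clients in close touch with their coach are more likely to count as users, and those in little touch are more likely to drop out of the numerator. If non-users have fewer contacts, the ratio rises even when enrolled clients as a whole have no more contact than anyone else.

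At stake is a primary pilot outcome that feeds the Go/No Go decision. With at most 40 pilot clients, reclassifying a few of them could change whether the target is met. While two wordings stand, the choice between them could also be made after the data are seen.

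**Working it through.** The 20% target is a threshold. It is not derived from other inputs, so there is no figure of the plan's own to reproduce. The check asks how large the use-based ratio can become when enrollment brings no gain.

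**Inputs from the article:** target ratio 1.20; at most 40 pilot clients (Sample Size and Planned Recruitment Rate).

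**Assumptions, because the article gives no figures:** the share *u* of enrolled clients who use the app; the ratio *k* of users' contact rate to that of enrolled non-users; the base contact rate; the number of nonparticipants.

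**Formula.** Set the mean of all enrolled clients equal to the nonparticipant mean, so that enrolled against nonenrolled is exactly 1.00. Then

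users / nonparticipants = *k* / (*uk* + 1 − *u*).

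This reaches 1.20 when *k* ≥ 1.2(1 − *u*) / (1 − 1.2*u*). As *k* grows the ratio approaches 1/*u*, so 1.20 is out of reach once *u* > 1/1.2 = 83.3%.

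| Share using the app | *k* needed for 1.20 |
|---|---|
| 30% | 1.2 × 0.7 / 0.64 = 1.31 |
| 50% | 1.2 × 0.5 / 0.40 = 1.50 |
| 60% | 1.2 × 0.4 / 0.28 = 1.71 |
| 70% | 1.2 × 0.3 / 0.16 = 2.25 |
| 80% | 1.2 × 0.2 / 0.04 = 6.00 |
| above 83.3% | not attainable |

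**Worked case at 60% use.** Take 40 enrolled clients: 24 users at 4.8 contacts a month and 16 non-users at 2.8, so *k* = 4.8/2.8 = 1.71. The enrolled mean is (24 × 4.8 + 16 × 2.8)/40 = 4.0. With nonparticipants also at 4.0, enrolled against nonenrolled is 4.0/4.0 = 1.00, while users against nonparticipants is 4.8/4.0 = 1.20.

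**Simulation with sampling variation.** There were 20,000 runs per setting with 40 enrolled clients. The assumptions were 120 nonparticipants, a mean of 10 contacts, gamma-Poisson counts, use correlated about 0.7 with (log) engagement, and no true gain. Each cell gives the mean ratio and the share of runs with a ratio of at least 1.20. CV is the between-client coefficient of variation.

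| CV | By enrollment | By use, 50% using | By use, 70% using | By use, 85% using |
|---|---|---|---|---|
| 0.4 | 1.00; 2% | 1.22; 53% | 1.13; 27% | 1.07; 11% |
| 0.6 | 1.00; 6–7% | 1.31; 73% | 1.19; 45% | 1.10; 23% |
| 0.8 | 1.01; 11–12% | 1.40; 78% | 1.24; 55% | 1.12; 32% |

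The 83.3% limit applies to the ratio when the enrolled and nonparticipant means are exactly equal. In a sample this small chance can still carry the ratio past 1.20 at higher use, as the last column shows.

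**The case against.** The strongest reply is that using the app simply means being in the study. There is good support for it:

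- The Statistical Analysis Plan section uses both terms for one target in one sentence.
- The Results section describes the app arm of the later randomized trial as clients using the app.
- App access is restricted to participants and the research team, and onboarding includes a sample message from the coach.
- No section plans a split into users and non-users.

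This makes the shorthand plausible, but no sentence states it. Table 5 lists 40 pilot clients under Peer PLUS use, but only as a maximum count. The feasibility section files the target under app usage statistics, which points the other way. These are conflicting statements of a primary outcome within the article, so they are not a detail that can be left to an analysis plan.

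Four stronger readings are tempting, and the article does not support them:

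- **Enrolled non-users move into the comparator.** Table 2 read alone could suggest this. With an assumed 200 nonparticipants, the worked case would become 4.8 / [(200 × 4.0 + 16 × 2.8)/216] = 4.8/3.91 = 1.23. But the Abstract, the feasibility section and the Statistical Analysis Plan section all name nonenrolled or nonparticipating clients as the comparator.
- **The ratio is biased upward whatever the app does.** The bias requires non-users with fewer contacts, and it fades as use approaches 100%.
- **The pilot expressly permits no use at all.** The sentence on no minimum usage is in the Beta Testing Procedure. For the pilot, non-use is an inference from the instructions to use the app naturally and when possible.
- **A user-only ratio would mispredict the R33 trial.** That trial's primary outcome is the Substance Use Recovery Evaluator (SURE) score against a control app. Neither form of the contact ratio predicts it.

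**Conclusion.** The concern holds as an inconsistency in the definition of a primary Go/No Go milestone, with a bias that follows if the use-based wording is applied. It does not show that the authors intend to exclude enrolled non-users.

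The size depends on how many enrolled clients do not use the app and how much less contact they have. At 50% to 70% use, a user to non-user contact ratio of 1.5 to 2.25 is enough to show 20% more contacts with no gain among enrolled clients. At 80% use it takes a sixfold ratio, and above about 83% this mechanism alone is not enough. The article reports neither use rates nor contact rates, so all of these are assumed values that show what is possible, not what is expected.

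Classing by enrollment removes selection on use only. Enrollment is still selected by the coach's judgment, client interest, smartphone access and time in the program. An enrolled-against-nonenrolled ratio of 1.20 would therefore still not be a randomized estimate of the app's effect.

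**What to change.** Use the Abstract's definition everywhere. In Table 2, the feasibility section and the Statistical Analysis Plan section, state that the milestone compares all enrolled pilot clients, counted from enrollment whatever their app use, with nonenrolled (nonparticipating) clients. Say explicitly that enrolled clients who do not use the app stay in the enrolled group. If a user-only ratio is wanted, define use, report the ratio as descriptive, and state that it cannot trigger the milestone.

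The cost is a wording change in three places. New data collection should not be needed. Contacts with enrolled clients who do not use the app will not appear in the app log, but coaches record encounters in the client management system, which the Results section says is deployed across the whole PRC team. The Abstract has pilot testing and analyses continuing in 2026, so the definition can be settled before the analysis. The downside is that the reported ratio may be somewhat lower than a user-only ratio. The report should also say that the comparison is non-randomized and name the remaining sources of selection.
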